### Aim of the study

2.1

The objective of this study is to discover novel specific biomarkers associated with the pathogenesis of acne by analyzing metabolomics/molecular biomarkers and skin biophysical parameters between healthy individuals and patients with acne, to compare the differences in these biomarkers according to the severity of acne, and to explore the correlation between such biomarkers and various factors, such as acne symptoms, dietary habit, stress level, sleep pattern, and menstrual pattern.

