##### Participation of the population with acne vulgaris

2.3.1.1

Participants who will meet the following criteria will be included:1.Age of 19 to 35 years.2.Body mass index (BMI) of 18.5 to 23 kg/m^2^.3.Acne vulgaris [20 individuals with Korean Acne Grading System (KAGS) Gr 1 or 2; 20 individuals with KAGS Gr 3 or 4; and 20 individuals with over KAGS Gr 5).4.Voluntary participation in this clinical trial.

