### Sample size

2.7

The current study is a preliminary cross-sectional trial with the aims of discovering novel specific biomarkers in acne by investigating metabolomics/molecular biomarkers between healthy individuals and patients with acne, comparing the differences in these biomarkers according to the severity of acne, and exploring the correlation between the biomarkers and acne symptoms. In other words, this study is, to the best of our knowledge, the first of its kind and not intended to validate affirmatively the effects of certain interventions on acne, but rather to compare the biomarkers of patients with acne with those of healthy individuals. If the aims of the pilot study do not include any hypothesis tests, the power level of a test procedure is not a valid consideration for sample size.^[20]^ Moreover, in the metabolomics study design, a sample size of 3 to 5 per group may give useful preliminary data that can be used to design more elaborate and/or targeted metabolomics studies and the number of sample size for a metabolomics experiment depends on the biological variability associated with the system being studied compared with the analytical variability of the analytical system.^[21]^ Therefore, in this exploratory study, the number of patients to be included will be set to 40 healthy subjects (20 men and 20 women) and 60 patients with acne (30 men and 30 women) which enables the assessment of the difference in metabolomics/molecular biomarkers between healthy individuals and patients with acne including a respective 95% confidence interval, with sufficient precision according to the size of the metabolite kit with expert opinions in metabolomics, molecular biology, dermatology, and statistics.

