### Statistical methods

2.8

Data will be displayed as means ± standard deviations for continuous data or n (%) for categorical data. Statistical analyses will be conducted with a 95% confidence interval using the SPSS 21.0 (IBM SPSS Statistics, New York, NY). An independent *t* test will be performed for the comparison of specific biomarkers associated with the pathogenesis of acne by analyzing metabolomics/molecular biomarkers and skin biophysical parameters between the healthy subjects and participants with acne vulgaris. One-way analysis of variance will be performed for the comparison of the differences in these biomarkers among 3 groups (mild, Gr 1-2; moderate, Gr 3-4; severe, Gr 5-6), which we will classify in accordance with the severity of acne using the KAGS. The correlation between the biomarkers and various factors, such as acne symptoms, dietary habit, stress level, sleep pattern, and menstrual pattern, will be examined using the Pearson correlation test. The mean value of a variable will be used in place of the missing data value for that same variable.

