## Discussion

3

Although accumulating evidence underlines the role of Western diet, stress, and smoking in the pathogenesis of acne, the pathogenesis and aggravating factors of acne are not yet fully elucidated. Therefore, the metabolomics/molecular biomarkers could be an issue when discussing acne management with patients.

This will be the first protocol that would discover new diagnostic biomarkers in acne by analyzing metabolomics/molecular biomarkers and skin biophysical parameters between healthy individuals and patients with acne, compare the differences in these biomarkers according to the severity of acne, and explore the correlation between these biomarkers and various factors. In this study, we will analyze the molecular biomarkers, including zinc, calcium, and ROS, as well as existing known inflammatory cytokines and chemokines, and targeted and untargeted metabolite biomarkers, such as steroidal hormones, fatty acids, and endogenous small metabolites closely related to energy metabolism and lipid/steroid biosynthesis in terms of systems biology. We will also use the skin biophysical measurement devices Sebumeter SM815, Skin-Thermometer ST500, and Reviscometer RVM600 and questionnaires that would include general sociodemographic information, personal habits, anthropometric measurements, pregnancy, menstrual pattern and history, use of oral contraceptives, history of adolescence acne, history of acne in relatives, relevant comorbidities, acne pattern identification, and stress level.

Several methodological limitations within this study warrant further discussion. First, only young adults will be studied, and the sample size was decided in accordance with the size of the metabolite kit with expert opinions in metabolomics, molecular biology, dermatology, and statistics and not a power analysis. Second, diet tracking will not be performed. Third, this study has a cross-sectional design; because of the nature of this study design, interpretations of the results will be limited.

Despite these limitations, this study could be helpful in providing new diagnostic human biomarkers in acne and correlation between human biomarkers and patterns of acne. The findings of this trial may have important implications for the new approach of personal individualized therapy by identifying and differentiating the treatment methods of acne according to the biological and metabolic biomarkers based on human blood samples and patterns of acne.

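### The three severity bands are ordered, but the only test named for them is an omnibus ANOVA; a pre-specified linear trend beside it would be a cheap improvement

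*Protocol article*

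**What the plan says.** The aim in section 2.1 includes "to compare the differences in these biomarkers according to the severity of acne". Section 2.8 names one test for this: "One-way analysis of variance will be performed for the comparison of the differences in these biomarkers among 3 groups". It defines the groups as "mild, Gr 1-2; moderate, Gr 3-4; severe, Gr 5-6), which we will classify in accordance with the severity of acne using the KAGS". The inclusion criteria for patients (section 2.3.1.1) recruit by band, with 20 at Gr 1 or 2 and then "20 individuals with KAGS Gr 3 or 4; and 20 individuals with over KAGS Gr 5", which makes the 60 patients planned.

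No trend test, planned contrast or ordinal analysis is named for the bands. A separate sentence in section 2.8 plans Pearson correlations: "The correlation between the biomarkers and various factors, such as acne symptoms, dietary habit, stress level, sleep pattern, and menstrual pattern". It does not say whether KAGS grade or lesion counts stand for acne symptoms there.

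No alpha is stated as such; the nearest statement is "Statistical analyses will be conducted with a 95% confidence interval". Section 2.7 sets power aside ("the power level of a test procedure is not a valid consideration for sample size"), and the Discussion says that the sample size was decided "with expert opinions in metabolomics, molecular biology, dermatology, and statistics and not a power analysis".

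**The concern.** The bands come from an ordered scale, and recruitment fixes equal numbers in each, so the severity axis is built into the sampling. The omnibus F test has 2 numerator degrees of freedom and gives the same result if the labels mild, moderate and severe are exchanged in any way. It therefore makes no use of the order.

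Two things follow. A marker that changes steadily with severity is detected less often than the same 60 samples would allow. And a significant F does not say whether the marker rises, falls or peaks in the middle band. In a screen of cytokines, hormones, fatty acids and untargeted metabolites, a result of the last kind could be reported as related to severity with no stated rule on direction.

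**Working it through.** The article gives no power, effect size or SD for this comparison, so it has no figure to reproduce. Only the group arithmetic can be checked: 3 × 20 = 60, which agrees with the planned number of patients.

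**Inputs from the article.** Three bands with n = 20 each, reading the top recruitment band as the Gr 5-6 group of section 2.8. Denominator df = 60 − 3 = 57. Two-sided alpha of 0.05 is inferred from the 95% confidence level.

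**Assumed inputs.** Within-band SD = 1; band means (0, m, d), where d is the severe-minus-mild difference in SD units and m the moderate mean.

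**Formulas.**
- Omnibus ANOVA: non-central F with 2 and 57 df, λ = n·Σ(μᵢ − μ̄)².
- Linear contrast (−1, 0, +1): non-central t with 57 df, δ = d / √(2/n), so δ² = n·d²/2 = 10·d².

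For equally spaced means (0, d/2, d), λ = 20 × d²/2 = 10·d², the same as δ². Both tests then carry the same signal, but the F test spreads it over 2 df.

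**Equally spaced means.**

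| d (SD) | λ = δ² | ANOVA | Linear contrast | Gain (points) |
|---|---|---|---|---|
| 0.3 | 0.9 | 12.0% | 15.4% | 3.4 |
| 0.5 | 2.5 | 26.1% | 34.3% | 8.2 |
| 0.6 | 3.6 | 36.1% | 46.2% | 10.1 |
| 0.8 | 6.4 | 58.9% | 70.1% | 11.2 |
| 0.9 | 8.1 | 69.9% | 79.9% | 10.0 |
| 1.0 | 10.0 | 79.3% | 87.5% | 8.1 |
| 1.2 | 14.4 | 92.2% | 96.2% | 4.0 |

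(Gains are taken before rounding.) The largest gain is 11.3 points, near d = 0.74. A simulation of 20,000 runs at d = 0.9 gave 69.6% for ANOVA and 79.7% for a correlation with the band score. At d = 0.8 the ANOVA would need 26 per band to match the contrast (25 gives 69.8%, 26 gives 71.7%), which is 3 × 6 = 18 more patients.

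**Other shapes.** The contrast uses only the mild and severe means, so its power depends on d alone.

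| Band means (SD) | λ | ANOVA | Linear contrast |
|---|---|---|---|
| (0, 0.2, 0.8), uneven rise | 6.93 | 62.6% | 70.1% |
| (0, 0, 0.8), step | 8.53 | 72.3% | 70.1% |
| (0, 1.2, 0.8), moderate above severe | 14.93 | 93.1% | 70.1% |
| (0, 0.8, 0.2), near-hump | 6.93 | 62.6% | 9.5% |

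For a step pattern, the contrast is 0.6 points better at d = 0.5 and 2.2 to 2.6 points worse at d = 0.8 to 1.0. When the moderate mean lies beyond the severe mean by a quarter or a half of d, at d = 0.9, the contrast is 11.8 or 17.5 points worse.

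**Direction when nothing differs.** If a marker has no relation to severity, the three sample means are equally likely to fall in any of 6 orders, of which 2 are monotone. So 4/6 = 67% of false-positive omnibus results would show a non-monotone order.

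**The case against.** The strongest reply is that the plan contains no error. A reader might infer that the study is looking for a graded relation and that the ANOVA therefore answers the wrong question. The article does not say so. It speaks of comparing differences by severity and never of a trend, a gradient or a dose-response, and a one-way ANOVA is a valid answer to that. This part of the objection stands.

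It also stands that no fixed power cost can be attached to the plan. The gain needs an assumed shape and size. It is small for weak or strong effects, vanishes or reverses for a step, and becomes a large loss when the moderate band lies outside the mild-severe range.

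Nor does the contrast on its own prove a steady rise. It gives the moderate mean zero weight, so its power is 70.1% for (0, 0.4, 0.8) and equally 70.1% for the non-monotone (0, 1.2, 0.8). That is why the band means must be read with it and the ANOVA kept.

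Two further replies carry less weight. The Pearson correlation with acne symptoms may recover some of the ordering, but KAGS grade is not named there. An unseen analysis plan may specify contrasts, in which case the request is already met; as the article stands, the omnibus test is the only one named for the bands.

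Finally, the study is exploratory and claims no power. That lowers the importance of the point. But since kit size and expert opinion fix the sample, the choice of analysis is one of the few ways left to gain sensitivity from it.

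**Conclusion.** The point holds as a minor, cheap improvement. The bands are ordered, and the one test named for them uses neither the order nor the direction. For roughly linear gradients, a trend test beside it would gain about 8 to 11 points of power at severe-minus-mild differences of 0.5 to 1.0 SD, and about 3 to 4 points at 0.3 or 1.2 SD. These figures rest on 20 evaluable patients per band, equal within-band SD, two-sided alpha of 0.05 per marker and equally spaced means; the effect sizes are assumptions.

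The documents do not support the stronger conclusions that the ANOVA is invalid, that the plan loses a set 10 points of power, or that the contrast should displace the ANOVA as the main severity test. Displacing it would trade power for step and non-monotone patterns against power for linear ones, and nothing in the article says which shape is expected.

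**What to change.** In section 2.8, keep the omnibus ANOVA and pre-specify beside it a 1-df linear trend across the bands, either as the contrast (−1, 0, +1) from the same model or as a regression on KAGS grade. (The power figures here are for the contrast only.) Report the slope with its 95% CI and the three band means. With the contrast, the slope per band is half the severe-minus-mild difference. Call a marker severity-graded only when the trend is supported and the band means are in monotone order; report other significant ANOVA results as differences between bands without a graded claim.

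The cost is a sentence or two of text and one more test per marker in a screen that already runs many. No new patients, samples or software are needed. The trend test has little power for hump-shaped patterns, which the retained ANOVA covers. The labelling rule will be met somewhat less often than the trend test alone is significant, because it adds a condition.

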#### Questionnaire

2.5.1

The participants will complete a questionnaire that would include general sociodemographic information (e.g., age and sex), personal habits (e.g., smoking, alcohol consumption, sleep pattern, and dietary habits),^[4,13]^ anthropometric measurements (e.g., height, weight, and BMI), pregnancy, menstrual pattern and history, use of oral contraceptives, history of adolescence acne, history of acne in relatives, relevant comorbidities (e.g., polycystic ovary syndrome, hirsutism, type II diabetes, and thyroid disease), acne pattern identification,^[14]^ and stress level during the last month, which will be self-assessed in accordance with the stress response inventory.^[15]^

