#### Exploring biomarker with metabolomic profiling

2.5.4

This study will apply MS-based metabolomic profiling studies for the detection and identification of potential metabolic biomarkers for acne in the participants’ serum. The liquid chromatography-mass spectrometry system will consist of a Thermo Scientific Vanquish ultra-high-performance liquid chromatography (UHPLC) system (Thermo Fisher Scientific, Sunnyvale, CA) with a triple ToF 5600+ mass spectrometer system (Triple ToF MS) (SCIEX, Foster City, CA) for untargeted metabolite analysis. The UHPLC system with a QTRAP 3200TM (hybrid triple quadrupole/linear ion trap) mass spectrometry system (SCIEX, Foster City, CA). The analytical methods will be developed and optimized for targeted and untargeted analyses of metabolites, such as steroidal hormones (dehydroepiandrosterone, androstenedione, testosterone, dihydrotestosterone, estrone, and estradiol), fatty acids (oleic acid; cis, elaidic acid; trans, palmitic acid; saturated), and endogenous small metabolites closely related to energy metabolism and lipid/steroid biosynthesis. Statistical techniques will be used to investigate the particular metabolic changes and entire network of the metabolic pathway profile.

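### The biomarker–lifestyle correlations use a plain Pearson test in a half-male, half-female sample, so for markers that differ by sex the coefficient mixes sex differences with the within-sex link

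*Protocol article*

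**What the plan says.** Section 2.8 (Statistical methods) sets out the analysis of "The correlation between the biomarkers and various factors". It lists "various factors, such as acne symptoms, dietary habit, stress level, sleep pattern, and menstrual pattern" as the variables to be set against the biomarkers, and says that the relation "will be examined using the Pearson correlation test". It names no covariate, stratum or partial correlation. The same section sets the general error level: "Statistical analyses will be conducted with a 95% confidence interval".

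Section 2.7 (Sample size) fixes the recruitment as "40 healthy subjects (20 men and 20 women) and 60 patients with acne (30 men and 30 women"). Men are therefore half of the controls, half of the patients and half of the whole sample.

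Section 2.5.4 (metabolomic profiling) includes among the targeted metabolites "steroidal hormones (dehydroepiandrosterone, androstenedione, testosterone, dihydrotestosterone, estrone, and estradiol"). Section 2.5.1 (Questionnaire) collects "general sociodemographic information (e.g., age and sex"), so sex is available for every participant.

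No section of the article stratifies or adjusts any analysis by sex. Exploring these correlations is a stated aim in the Introduction and in section 2.1.

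**The concern.** A Pearson coefficient taken over a mixture of two groups reflects two things: how the variables move together inside each group, and how the group means differ. With equal numbers of men and women, the second part carries the most weight it can. Several of the steroids can be expected to differ in level between men and women. For those markers the planned coefficient does not answer the question asked, which is whether a person's hormone level goes with diet, stress or sleep.

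The harm takes two forms, which arise under different conditions:

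- **The factor also differs by sex.** The pooled coefficient gains a component that comes from sex alone. It can produce a correlation where none exists within either sex, or inflate, cancel or reverse one that does.
- **The factor does not differ by sex.** No false link arises, but the between-sex spread of the marker enlarges the denominator and a true within-sex link is diluted.

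The equal sex quotas protect the comparison of patients with controls, because sex is balanced across those two groups. They give no such protection to the correlations.

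**Working it through.** **Inputs from the article**
- Men 20 + 30 = 50; women 20 + 30 = 50; n = 100 (section 2.7).
- Plain Pearson test (section 2.8); two-sided 5% is assumed from the 95% interval stated there.
- No stated figure can be reproduced. The article gives no effect size, SD or sex difference, and its Discussion says that the sample size rests on kit size and expert opinion, "and not a power analysis".

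**Assumptions**
- dB and dL are the male–female mean differences in biomarker and factor, in within-sex SDs. They are varied over a range.
- The within-sex SDs and the within-sex correlation r_w are equal in men and women, with normal errors.

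**Formula for a 50:50 mix**

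r_pooled = (r_w + dB·dL/4) / √[(1 + dB²/4)(1 + dL²/4)]

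Rejection rate by Fisher's z: with z = atanh(r_pooled)·√97, the rate is Φ(z − 1.96) + Φ(−z − 1.96). The critical |r| at n = 100 is 0.197.

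**1. False links (r_w = 0)**

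Example with dB = 3 and dL = 0.5: r = 0.375 / √(3.25 × 1.0625) = 0.375 / 1.858 = 0.20. Rejection is 52% by Fisher's z and 53% to 54% by simulation.

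Induced r, with rejection by Fisher's z in brackets:

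| Marker gap dB | dL = 0.2 | dL = 0.3 | dL = 0.5 |
|---|---|---|---|
| 1 | 0.04 (7%) | 0.07 (10%) | 0.11 (19%) |
| 2 | 0.07 (11%) | 0.11 (18%) | 0.17 (40%) |
| 3 | 0.08 (13%) | 0.12 (23%) | 0.20 (52%) |
| 4 | 0.09 (14%) | 0.13 (26%) | 0.22 (58%) |

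Simulated rejection for dL from 0.3 to 0.7: 10% to 32% at dB = 1, 18% to 66% at dB = 2, and 27% to 87% at dB = 4. At dL = 0 the rate is 5% whatever dB is.

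**2. Dilution (dL = 0)**

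The formula reduces to r_w / √(1 + dB²/4). For r_w = 0.40:
- dB = 2: 0.40 / √2 = 0.28, power 82%
- dB = 3: 0.40 / √3.25 = 0.22, power 60%
- dB = 4: 0.40 / √5 = 0.18, power 43%

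Power with sex adjustment is about 99%.

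**3. Both gaps present (dB = 3, dL = 0.5)**
- r_w = +0.30: (0.30 + 0.375) / 1.858 = +0.36, inflated.
- r_w = −0.30: (−0.30 + 0.375) / 1.858 = +0.04, cancelled and slightly reversed. Simulated rejection is about 6%, against about 86% with sex adjustment.

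**4. Check of the remedy**

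In simulation, the partial correlation given sex (97 df) rejects about 5% of the time when r_w = 0, for every pair of gaps tried. It recovers a mean r of about 0.30 with about 86% power when r_w = 0.30.

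**The case against.** The strongest counter-argument is that the size is assumed. Nothing in the article says that stress, diet or sleep differ between men and women, or by how much any marker does. That stands. A reader might infer that the hormones are bound to appear linked to every lifestyle factor. The documents do not support this: a factor gap of 0.2 SD induces an r of at most 0.09 over the range shown, and a gap of zero induces none.

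A reader might also infer that real within-sex links are always diluted, or lost altogether. Neither follows. Dilution is exact only when the factor does not differ by sex; otherwise a link can equally be inflated. Even at a marker gap of 4 SD, a true 0.40 is still detected in about 43% of studies.

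The scope is also limited. The harm is confined to markers that differ by sex, and no sex gap is shown for the cytokines, zinc, calcium or the skin measures. Menstrual pattern concerns women only, and section 2.5 does not collect acne pattern identification in controls, so not every correlation uses all 100 participants. The patient-versus-control t test is not confounded by sex.

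Finally, the article is condensed, does not say outright that men and women are pooled, and calls the study preliminary and exploratory. An unseen analysis plan could stratify. But the article names the test, and that test has no sex term. Exploratory status lowers the stakes without justifying a confounder that a recorded variable can remove.

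**Conclusion.** The point holds in conditional form. For markers that differ by sex, notably the sex steroids, the test stated in section 2.8 mixes the between-sex difference with the within-sex link. With no within-sex link and n = 100, false rejection runs from about 10% to 87% for marker gaps of 1 to 4 SD and factor gaps of 0.3 to 0.7 SD. It is 7% to 14% at a factor gap of 0.2 SD and the nominal 5% at zero. The dilution figures apply only where the factor has no sex gap.

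All of this rests on assumed gaps, equal within-sex SDs and a two-sided 5% level. It bears on the correlations of diet, stress and sleep with sex-dependent markers. It does not bear on the main comparison of patients with controls. The change should be made, because these correlations are a stated aim and the remedy needs no new data.

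**What to change.** In section 2.8, replace the plain Pearson test with one of two options: a partial correlation (or regression) given sex, or correlations computed within each sex and then combined. Show the six steroids separately for men and women, since a single adjusted coefficient assumes the same link in both sexes. Analyse menstrual pattern in women only.

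The cost is one clause in the text and one degree of freedom. The sex-specific tables will have wider intervals. With n = 50 per sex, the 95% half-width on Fisher's z scale is 1.96/√47 = 0.29, against 1.96/√97 = 0.20 for all 100.

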## Abstract

Acne is a multifactorial dermatosis, which is influenced not only by hormones but also by the biochemical relationship between them and the pilosebaceous unit. Inflammatory cytokines, chemokines, active oxygen, and zinc are known to be associated with the development of acne. Further, steroid metabolism is known as one of the important factors related to sebum secretion and comedone formation in acne. However, there is a lack of studies comparing these human biomarkers between healthy individuals and patients with acne. In particular, no study has investigated the relationship between human biomarkers and patterns of acne yet.

The purpose of this study is to investigate diagnostic human biomarkers in acne by comparing the biological and metabolic biomarkers between healthy individuals and patients with acne and identify the relationship between human biomarkers and patterns of acne.

This study is a protocol for a cross-sectional study. Forty healthy participants and 60 patients with acne will be recruited at 1 center. We will collect their blood samples and analyze the molecular biological and metabolic biomarkers (cytokines, chemokines, reactive oxygen species, corticotropin-releasing hormone, zinc, amino acid, 1-carbon metabolite, lipid metabolite, etc.). Further, we will administer questionnaires regarding their diet, sleep, stress, and other factors relating to acne and measure their skin elasticity.

The study protocol was approved by the Institutional Review Board of Oriental Medical Hospital at Kyung Hee Medical Center (KOMCIRB-161118-HR-062). Written informed consent will be obtained from all the participants. The trial was registered in the Clinical Research Information Service, Republic of Korea: KCT0002212.

This trial will provide evidence regarding diagnostic human biomarkers in acne and the relationship between the human biomarkers and patterns of acne.

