## Introduction

1

Acne vulgaris is a common chronic inflammatory dermatosis that manifests as papules, pustules, nodules, and cysts in the pilosebaceous units on the face, chest, and back.^[1,2]^ It is one of the most common diseases during adolescence, affecting more than 85% of adolescents.^[3]^ However, according to lifestyle factors, such as diet, occupation, and stress, the incidence of adult female acne, which starts after 25 years of age, is increasing.^[4]^ Acne is caused by multiple factors, such as increased sebum overproduction, abnormal cornification of the sebaceous follicular duct, colonization of the intrafollicular duct by *Propionibacterium acnes*, and inflammation.^[5,6]^ Genetic predispositions, hormonal abnormalities, immunological disorders, and psychological, environmental, and even iatrogenic factors may contribute to the formation of acne.^[7]^ Acne remains a rare disease in non-Westernized societies; however, the adoption of Western lifestyles increases the incidence of acne. Recent studies have reported that the Western diet is over-stimulated with the mammalian target of rapamycin complex-1 (mTORC1) signaling exaggerated cell growth and proliferation and mTORC1-mediated insulin resistance due to increased milk/dairy protein consumption with high glycemic loads and abundant amounts of branched chain amino acids,^[8,9]^ increased nutrient-sensitive kinase mTORC1 activity, and decreased nuclear levels of forkhead box class O1 transcription factor, which might aggravate or promote acne development.^[2,8]^

Although Western diet,^[10]^ stress,^[11]^ and smoking^[12]^ are factors that worsen acne, the exact etiology is still unknown. There is a lack of studies comparing these human biomarkers between healthy individuals and patients with acne, and no study has investigated the relationship between human biomarkers and patterns of acne yet.

The objective of this research is to determine the diagnostic specific human biomarkers in acne by comparing the molecular biological and metabolomics biomarkers between healthy control subjects and patients with acne, identify the relationship between human biomarkers and patterns of acne, and explore the correlation between biomarkers and various lifestyle factors affecting acne.

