### Outcome measures

2.5

According to the schedule depicted on Table 1, we will use a series of outcome measures. There will be no difference in the outcomes measured between the patients with acne vulgaris and healthy subjects, except for the pattern identification related to acne symptoms. Facial photoshoot will be performed only on the participants with acne vulgaris. Five milliliters of whole blood will be collected in both patients with acne and healthy participants. The sera will be obtained from the whole blood via centrifugation 30 to 60 min after blood sampling.

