#### Acne severity using the KAGS

2.5.2

Acne severity is defined in accordance with the KAGS shown in Table 2^[16]^ using photographs limited to the face to help with the assessments. A Lumix DMC-LX2 digital camera (Panasonic, Osaka, Japan) will be used to photograph the front and both sides of each patient's face, so that the inflammatory and noninflammatory lesions can be counted independently.

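### One Pearson test is fixed for all biomarker–factor associations whatever the factor's scale, without adjustment for acne status or sex, and section 2.8 does not name the acne-pattern objective

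*Protocol article*

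**What the plan says.** Section 2.8 (Statistical methods) assigns a t test to acne versus healthy, one-way ANOVA to the three severity bands, and a single method to everything else: the factors "such as acne symptoms, dietary habit, stress level, sleep pattern, and menstrual pattern, will be examined using the Pearson correlation test". The same section recognises categorical variables, but only for display, as "or n (%) for categorical data".

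The Abstract gives as a purpose of the study to "identify the relationship between human biomarkers and patterns of acne". The Introduction keeps this apart from the lifestyle question: "identify the relationship between human biomarkers and patterns of acne, and explore the correlation between biomarkers and various lifestyle factors affecting acne". The Discussion again lists patterns among the expected contributions. Section 2.1 (Aim of the study) and section 2.7 (Sample size) do not mention patterns; they speak of acne symptoms.

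On the variables themselves:
- Pattern identification is collected in patients only. Section 2.5 says outcomes are the same in both groups "except for the pattern identification related to acne symptoms".
- Section 2.5.1 lists "personal habits (e.g., smoking, alcohol consumption, sleep pattern, and dietary habits") as questionnaire topics, with no scale given.
- Stress comes from an inventory: "stress level during the last month, which will be self-assessed in accordance with the stress response inventory".
- Section 2.5.2 provides photographs of patients "so that the inflammatory and noninflammatory lesions can be counted independently".
- Section 2.3.1.2 requires control women to have had regular cycles over the preceding 3 months. The acne inclusion criteria contain no such requirement.
- Section 2.7 fixes 40 controls (20 men, 20 women) and 60 patients (30 men, 30 women).

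**The concern.** There are three linked problems.

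1. **Scale.** A Pearson coefficient needs a factor whose numerical values mean something. On a nominal factor with three or more levels, its size and sign depend on which category is called 0, 1 or 2. The plan makes no allowance for this.

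2. **Patterns.** The Abstract says that no study has yet examined biomarkers against patterns of acne, so this is one of the study's main claims to novelty. Read literally, section 2.8 leaves it in one of two positions. If patterns do not count as acne symptoms, the section names no test for them. If they do, Pearson is applied to what is, by its name, a classification.

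3. **Mixing of groups.** The study looks for biomarkers that differ by acne status, and the Introduction names diet and stress as acne-related. The biomarker panel includes sex hormones. Acne status and sex are both set by quota. An unadjusted coefficient for a factor measured in everyone can therefore arise only because both variables differ between patients and controls, or between men and women.

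At stake is whether the third objective yields coefficients that can be interpreted.

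**Working it through.** **The plan's own figures.** The document gives no effect size, SD or power, and the Discussion says the sample size does not come from a power analysis. Only the sums can be checked: 20 + 20 = 40, 30 + 30 = 60, 3 × 20 = 60, 40 + 60 = 100, and women 20 + 30 = 50. These agree. All effect sizes below are assumptions made for illustration.

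**Check 1: dependence on category numbering.** Assume 60 patients in three nominal patterns of 20, within-pattern SD 1, and one pattern shifted by 1 SD.
- Variance of the pattern means: (1/3)(2/3) = 0.222. Total variance: 1.222.
- Strength of association free of coding: eta = sqrt(0.222/1.222) = 0.43.
- Codes 0, 1, 2 have variance 2/3, so SD 0.816.
- Shifted pattern coded 1: covariance = 1/3 − 1 × 1/3 = 0, so r = 0.00.
- Shifted pattern coded 2: covariance = 2/3 − 1 × 1/3 = 1/3, so r = 0.333/(0.816 × 1.106) = 0.37. Coded 0, it is −0.37.

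In 5,000 simulated studies at the 5% level, one-way ANOVA rejected in 90%. Pearson rejected in 3% when the shifted pattern was coded in the middle and in 87% when it was coded at an end. With four patterns of 15, one shifted by 1 SD, |r| runs from 0.10 to 0.31 by numbering alone, against an eta of 0.40.

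**Check 2: correlation produced by acne status alone.** Let a fraction p belong to one group and q = 1 − p to the other, let the two variables shift by d1 and d2 SDs, and let them be unrelated within groups. Then

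r = pq·d1·d2 / sqrt[(1 + pq·d1²)(1 + pq·d2²)].

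With p = 0.6, pq = 0.24 and n = 100, the chance of a significant r (two-sided 5%) follows from Fisher's z, with mean atanh(r) × sqrt(97).

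| Assumed shift in both variables | r | Fisher z mean | Significant |
|---|---|---|---|
| 0.5 SD | 0.06/1.06 = 0.057 | 0.56 | about 9% |
| 1 SD | 0.24/1.24 = 0.194 | 1.93 | 49% |
| 1.5 SD | 0.54/1.54 = 0.351 | 3.61 | 95% |

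**Check 3: the same through sex.** With p = 0.5, pq = 0.25:
- Hormone shift 4 SD, factor shift 0.5 SD: r = 0.5/sqrt(5 × 1.0625) = 0.217, significant in 58%.
- Hormone shift 2 SD, factor shift 0.5 SD: r = 0.25/sqrt(2 × 1.0625) = 0.171, significant in 40%.

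**Check 4: menstrual pattern.** Only 50 of the 100 participants can contribute. If the factor is cycle regularity, eligibility leaves it without variation among the 20 control women, so any irregular cycles belong to the 30 patients. Across all 50 women, regularity is then tied to acne status by design.

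**The case against.** The strongest objection is that the document never states that these factors are categorical. Sleep could be hours, diet a score, menstrual pattern a cycle length, and symptoms the lesion counts from the photographs. Stress is presumably a numeric score. Pearson on a two-level factor is the point-biserial correlation and is valid. All of this stands. A reader might infer that Pearson is wrong for the whole list, but the text does not support that. What remains is that the method is fixed without regard to scale, and that pattern identification looks like a nominal classification.

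A reader might also infer that the pattern objective is left with no valid analysis at all. That goes too far. Section 2.5 ties pattern identification to acne symptoms, the list in section 2.8 is open-ended, and the pattern instrument, which is not shown, may yield a numeric score per pattern. A fuller analysis plan may also exist. The objective is nevertheless unnamed in sections 2.1, 2.7 and 2.8, and the only method that could cover it is one that suits a classification badly.

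On confounding, section 2.8 does not say in so many words that all 100 participants are pooled, and covariates are often left to an analysis plan. Patterns and facial photographs come from patients only, so acne status cannot confound those analyses. Sex is balanced at half in each group, so it does not confound the comparison by acne status. It can still produce a correlation between a biomarker and a lifestyle factor.

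The shifts in the checks are assumed. A 4 SD sex difference could suit at most a few hormones. The percentages are not type I error rates, because the marginal correlation in those scenarios is truly non-zero. They show how often an association explained entirely by group or sex would be reported. The study's exploratory label lowers the stakes, but an exploratory coefficient must still be interpretable.

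**Conclusion.** The point holds in a limited form. Section 2.8 fixes one coefficient for factors of unstated and probably mixed scale. For a nominal factor with three or more levels, that coefficient is arbitrary: |r| is 0.00 or 0.37 on the same data structure in the three-pattern example. The pattern objective appears in the Abstract, Introduction and Discussion but not in sections 2.1, 2.7 or 2.8. As stated, the correlations are unadjusted, so for factors measured in both groups a coefficient can reflect acne status or sex alone. The size of this depends strongly on the assumed shift: it is minor at 0.5 SD (about 9% significant) and large at 1 to 1.5 SD (49% to 95%).

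The conclusion rests on pattern identification being a classification, which its name suggests but the document does not confirm, and on reading section 2.8 as written, with no restriction or covariates. It does not extend to the stress score, lesion counts or two-level items as regards scale. This is a cheap improvement to the plan and does not invalidate the study.

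**What to change.** Revise the correlation sentence in section 2.8 as follows:

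- State the scale of each factor (numeric, ordinal, two-level, nominal).
- For pattern identification and any other nominal factor, compare biomarkers across categories with ANOVA or a linear model. Run the pattern analysis in the 60 patients.
- Use Spearman for ordinal or skewed scores, and keep Pearson for numeric factors with a roughly linear relation.
- Adjust for or stratify by sex, and also by acne status wherever both groups are included.
- Limit menstrual analyses to the 50 women, and note that control women must have regular cycles, so information on regularity within a group can come only from the 30 women with acne.
- Name the pattern objective in sections 2.1, 2.7 and 2.8 so that it agrees with the Abstract, Introduction and Discussion.

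No new data or software are needed. The cost is a few degrees of freedom (for example, two for acne status and sex, and two in place of one for a three-level pattern) and slightly more analysis work.
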